#### Primary outcome

Prolonged grief symptoms will be measured by ‘PG-13’. It consists of 13 items including 11 items assessing cognitive, behavioural and emotional symptoms during the past month, rated on a 5-point scale (not at all—several times a day/overwhelmingly). It also contains two items on duration and impairment (yes/no). PG-13 is scored by summarising the 11 items assessing symptoms. The total score ranges from 11 to 55, with higher scores indicates more severe PGD.^46^ The instrument is validated in a Swedish sample with bereaved parents and indicates satisfactory psychometric properties.^15^

#### Secondary outcomes

PTSD symptoms will be measured with the PTSD Checklist for DSM-5 at baseline and follow-up. It consists of 20 items describing symptoms of post traumatic stress. Participants rate on a 5-point scale (not at all—extremely, 0–4) to what extent they experience symptoms. The total score ranges from 0 to 80, and a higher score indicates more symptoms of post-traumatic stress.^47^ The Swedish version has shown satisfactory psychometric properties.^48^

Depression symptoms will be assessed with the Patient Health Questionnaire-9, which consists of nine items describing symptoms of depression. Participants rate to what extent they experience these symptoms during the last 2 weeks on a 4-point scale (not at all—nearly every day, 0–3). The total score ranges from 0 to 27, and a higher score indicates greater symptom severity.^49^

Quality of life will be measured with the Brunnsviken Brief Quality of Life Inventory. It consists of 12 items covering six different life domains. Participants rate on a 5-point scale (strongly disagree—strongly agree, 0–4), to what extent they agree with the statement. Total score ranges from 0 to 96. The instrument is validated in a Swedish sample.^50^

Grief-specific avoidance will be measured with the Depressive and Anxious Avoidance in Prolonged Grief Questionnaire (DAAPGQ). The questionnaire consists of nine items; five items measure depressive avoidance of activities and four items measures anxious avoidance of stimuli reminding of the loss. Participants rate on an 8-point scale (not at all true for me—completely true for me, 0–7) to what extent they experience the symptoms.^51^ The total score ranges from 0 to 72. The DAAPGQ was translated into Swedish by two grief researchers ([name]) at the Department of Neuroscience, Uppsala University in 2020 following European Organisation for Research and Treatment of Cancer (EORTC) guidelines.^52^

Grief-specific rumination will be measured with the Utrecht Grief Rumination Scale. The instrument consists of 15 items measuring different aspects of grief rumination. The participants rate on a 5-point scale (never-very often, 1–5) how often they experienced certain thoughts over the last month.^53^ Total scores range from 15 to 75 and generate an overall grief rumination score. The instrument is validated in a Swedish sample with bereaved parents and indicates satisfactory psychometric properties.^54^

Negative grief cognitions will be measured using a short version of Grief Cognitions Questionnaire (GCQ-18). It consists of 18 items, with statements regarding negative grief cognitions. Participants rate on a 6-point scale to what extent they agree with the statement (disagree strongly—agree strongly, 0–5). The total score ranges from 0 to 90^55^ and a higher score indicates stronger endorsement of negative cognitions.^56^ The GCQ was translated into Swedish by two grief researchers ([name]) at the Department of Neuroscience, Uppsala University in 2020 following EORTC guidelines.^52^

#### Users’ experiences: perceived satisfaction, helpfulness and adverse events

A questionnaire with 25 items (9 of them with free-text response) regarding the user experience of the app will be used after participants have had access to the app for 3 months. The questionnaire includes questions regarding for example the perceived helpfulness and benefits of the app, which sections and tools the participants used most commonly and why, and if any parts of the app could be improved. Adverse events are assessed through the question ‘Did the use of the app have any negative consequences?’ Participants who answered yes are asked to expand on this.

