**Methods and analysis:**

We will conduct a two-armed randomised waitlist-controlled trial. Parents living in Sweden, who lost a child between one and ten years ago, with elevated symptoms of prolonged grief, will be recruited to participate in the trial. The content of *My Grief* covers four main domains (Learn; Self-monitoring; Exercises; Get support) and builds on principles of CBT and the proven-effective *PTSD Coach* app. Participants in the intervention group will fill out online questionnaires at baseline and at 3, 6 and 12 months follow-ups, and the waitlist-controls at baseline and at 3 months. The primary outcome will be prolonged grief symptoms at the 3 months follow-up. Secondary outcomes are post-traumatic stress and depression symptoms, quality of life and cognitive behavioural variables (ie, avoidance, rumination, negative cognitions).

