The main aim of this study is to examine the effectiveness of the app *My Grief* as compared with a waiting list comparison in reducing symptoms of prolonged grief in bereaved parents. The primary hypothesis is that the parents in the intervention group will report decreased levels of prolonged grief symptoms after having access to the app. A second aim is to examine the effect of the app on related mental health problems (post-traumatic stress symptoms, depression symptoms and quality of life) and cognitive behavioural variables putatively explaining the effect of CBT techniques (ie, grief avoidance, grief rumination and negative grief cognitions). The secondary hypotheses are that the parents in the intervention group will report improved mental health (ie, lower symptom levels of depression and post-traumatic stress, higher quality of life) and lower grief avoidance, grief rumination and negative grief-related cognitions. A third aim is to assess participants experience of using the app, for example, perceived satisfaction helpfulness and adverse events.

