### Data collection

Participants complete questionnaires online. Time points for data collected via online questionnaires at t0 (baseline), t1 (3 months), t2 (6 months, only intervention group) and t3 (12 months, only intervention group) (table 1; figure 1). If the participant has not completed the online questionnaire, two reminder emails will be sent out for each measurement time point.

**Table 1 T1:** Time points for measurements

	Before baseline	t0, baseline	t1, 3 months	t2, 6 months*	t3, 12 months*
Consent	X				
Screening	X				
Sociodemographic		X			
Prolonged grief (Prolonged Grief Disorder-13)		X	X	X	X
Post traumatic stress (Post-traumatic Stress Disorder Checklist-5)		X	X	X	X
Depression (Patient Health Questionnaire-9)		X	X	X	X
Quality of life (Brunnsviken Brief Quality of Life Inventory)		X	X	X	X
Grief avoidance (Depressive and Anxious Avoidance in Prolonged Grief Questionnaire)		X	X	X	X
Grief rumination (Utrecht Grief Rumination Scale)		X	X	X	X
Negative grief cognitions (Grief Cognition Questionnaire-18)		X	X	X	X
Users’ experiences*			X		

*Only intervention group.

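### The adverse-event result has no waitlist comparator and covers only app-arm parents who return the 3-month form; a between-arm comparison of deterioration is not planned, although both arms supply the scores for it

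*Protocol article*

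**What the plan says.** The third aim, at the end of the Introduction, is to assess participants' experience of the app, for example "perceived satisfaction helpfulness and adverse events".

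The section on users' experiences gives the method: "Adverse events are assessed through the question" of whether app use brought any negative consequences, and a parent who says yes is invited to elaborate. The questionnaire that holds this item "will be used after participants have had access to the app for 3 months". In Table 1 (Data collection) it has a single mark, at t1, with the footnote "only intervention group". Questionnaires are completed online, and for those who have not answered "two reminder emails will be sent out for each measurement time point".

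No other collection of adverse events is described. The phone call after one week goes to the intervention group and checks that the app works. Ethics and dissemination offers referral, on request, to participants who report harm, but does not describe this as data capture.

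Symptom scores are collected in both arms. The abstract schedules "the waitlist-controls at baseline and at 3 months", and Table 1 lists PG-13, the PTSD checklist and PHQ-9 at t0 and t1. On all three a higher score is worse; for PG-13, "The total score ranges from 11 to 55, with higher scores indicates more severe PGD".

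Statistical methods and analysis plans regression models with condition, time and their interaction, and Cohen's *d* within and between groups with a 95% CI. It describes no analysis of the share of parents who get worse.

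**The concern.** Three features of the stated method limit what the adverse-event result can show.

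- **No comparator.** Only app users can answer a question about the consequences of using the app. Parents with elevated grief symptoms may get worse because of the app or because of the grief itself. Randomisation can separate the two; self-attribution in one arm cannot.
- **Responders only.** A parent who does not return the t1 form contributes nothing to the result. The missing-at-random assumption in the analysis section concerns missing follow-up data in the outcome models; nothing in the article extends it to this item.
- **Means only.** The between-arm analysis works on average scores, and an average can improve while a minority deteriorates.

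The point matters here because the app contains self-guided writing exercises that expose parents to the story of the loss, without professional feedback. The Ethics section itself expects that painful feelings and memories may be stirred up. Public release is tied to the app being shown effective.

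**Working it through.** **Inputs.** Total sample 154 and attrition 16% (Sample size); allocation 1:1 (Design); adverse-event item in the app arm at t1 only (Table 1). The documents give no rates of harm or deterioration, so those used below are assumptions.

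**1. The plan's own figure.** A two-group comparison with *f* = 0.25, α = 0.05 and power 0.80 needs 128 parents, 64 per arm. With 16% attrition, 64 / 0.84 = 76.2, rounded up to 77 per arm, or 154 in total. This reproduces the stated figure. It does so without the stated *r* = 0.50, but nothing below depends on that.

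**2. How many answer the item.** 77 × 0.84 = 64.7, about 65. The other 77 − 65 = 12 app-arm parents are unassessed.

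**3. What zero reports would mean.** The one-sided 95% upper bound for 0 of *n* is 1 − 0.05^(1/*n*).

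| Responders | Upper bound |
|---|---|
| 77 (all return) | 3.8% |
| 65 (16% attrition) | 4.5% |
| 58 (25% attrition, the ceiling the Discussion quotes for earlier studies of the similar app) | 5.0% |

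Most of the bound reflects the size of the arm; attrition adds less than a percentage point at 16%.

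**4. What non-return could hide.** Suppose 5% of responders say yes (assumed). If no non-returner was harmed, the whole-arm rate is 0.05 × 0.84 = 4.2%. If all were, it is 4.2% + 16% = 20.2%. These are extreme limits, not estimates.

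**5. Why the planned means do not answer the question.** Let a share *p* worsen by *a* points and the rest improve by *b* points on average. The mean still improves whenever *b* > *pa* / (1 − *p*). With *p* = 0.15 (assumed), 0.15 / 0.85 = 0.18, so the arm mean improves as long as the other 85% gain more than 0.18*a*.

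**6. What a comparison of deterioration could show.** With 64 per arm and a two-sided 5% test, power is approximately Φ{[√*n* |*p*₂ − *p*₁| − 1.96 √(2*p̄*(1 − *p̄*))] / √(*p*₁(1 − *p*₁) + *p*₂(1 − *p*₂))}. For 5% against 15%: [8 × 0.10 − 1.96 × 0.424] / 0.418 = −0.08, which gives 47%.

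| Waitlist vs app (assumed) | Power |
|---|---|
| 5% vs 15% | 47% |
| 5% vs 20% | 73% |
| 5% vs 25% | 90% |
| 10% vs 20% | 35% |
| 10% vs 30% | 82% |

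For 5% against 15% with 65 per arm, the 95% CI half-width for the risk difference is 1.96 × √[(0.0475 + 0.1275) / 65] = 0.10, so about 10 percentage points either way.

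Steps 3 and 6 treat parents as independent. Both parents of a child may take part and are then placed in the same arm (Design), so true precision may be somewhat lower.

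**The case against.** **The method fits the aim as worded.** The third aim concerns the experience of using the app, and only users can report on that. No between-arm comparison of harm is promised. This stands: the article does not contradict itself. It fixes a method whose result is limited.

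**The proposed table might sit in an unseen analysis plan.** Nothing in the article rules that out. But the instrument, the arm and the time point for adverse events are stated outright, and no analysis plan can create a waitlist answer to a question about app use.

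**The remedy does not reach non-returners.** Change from t0 to t1 also needs the t1 form. This stands in full; only reporting the number missing by arm touches that part.

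**The comparison would be imprecise**, and a null result could falsely reassure. This also stands, and it is why the analysis should be descriptive.

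A reader might infer more than the documents support:

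- *That the trial cannot compare harm between arms.* The adverse-event item cannot be compared, but symptom worsening can. The comparison is simply not planned.
- *That there will be no randomised evidence on harm.* The planned regressions compare the symptom scores between randomised arms and would show average worsening.
- *That the one-arm rate is too low, or that non-returners are those most likely to have been harmed.* The documents give no reasons for dropout. Stopping the app is not the same as not returning the form, because t1 is scheduled regardless of use. Self-attribution could also count ordinary grief as an effect of the app. The direction is not established.

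The protocol also excludes parents who report ongoing suicidal thoughts or psychosis, and cites earlier work that found no negative effects of the similar app. Neither supplies a comparator.

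**Conclusion.** The point holds in a limited form. The adverse-event result will be a one-arm, responder-only description: about 65 of 77 parents, with an upper bound of 4.5% if nobody reports harm. The planned models cover average worsening but leave open whether more parents deteriorate with the app than on the waitlist, a question that data already collected could address. The size rests on 77 per arm, the planned 16% attrition and independence between parents. The power figures rest on assumed deterioration rates. This is a worthwhile improvement to a stated method and does not put the primary analysis in doubt.

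**What to change.** 1. Pre-specify, as a descriptive harm analysis, the proportion in each arm whose PG-13, PHQ-9 or PTSD checklist score worsens from t0 to t1 by more than a pre-set reliable-change amount, with risk difference and 95% CI. Set the amount for each scale before outcome data are seen; it needs reliability figures that the article does not give, so their source should be stated.
2. Report this beside the app question, and label that question as one-arm and descriptive.
3. Give the number not returning the t1 form in each arm.
4. State that a null difference will not be read as evidence of safety.

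The cost is one extra table from data already collected, with no new assessments. The downside is low precision at about 65 per arm, and non-returners remain unassessed.

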### Data management

Study data are managed using REDCap electronic data capture tools^41^ hosted at Uppsala University. All data will be deidentified with a code number. The key to the codes will be stored separately, and is only available to members from the research group.

### Statistical methods and analysis

To examine intervention effects on the primary and secondary outcome variables, multiple regression models with the direct and interaction effect of condition ×time with the primary endpoint at 3 months follow-up will be performed. Missing data at follow-up will be handled under the assumption of missing at random. Data of all randomised participants will be included in the analyses (ie, intention-to-treat analysis). Cohen’s *d* and a 95% CI will be calculated to assess the within and between-group effect sizes at postintervention and follow-ups. Within group Cohen’s *d*’s, the standardised mean difference between the pre-assessment and the post-assessment for each group, will be calculated.^57^ Between groups Cohen’s *d*’s will also be calculated by dividing the differences between change scores of both groups across time by the pooled SD of both groups at baseline.^58^

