### Sample size

A required sample size of 154 participants was calculated in G*Power V.3.1, based on the primary research question. We considered a moderate effect size to be clinically meaningful (*f*=0.25), within a repeated measure analysis of variance, a desired power of 0.80, *α*=0.05, and an assumed strong association (*r*=0.50) between the preassessment and postassessment. The estimate includes an anticipated attrition rate of 16%.^42^

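### The condition × time contrast is valid, but adjusting for baseline PG-13 would raise power by about 8–10 points on the plan's own assumptions, at almost no cost

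*Protocol article*

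**What the plan says.** The protocol article, under Statistical methods and analysis, plans "multiple regression models with the direct and interaction effect of condition ×time with the primary endpoint at 3 months follow-up will be performed" for the primary and secondary outcomes. The same section obtains the between-group Cohen's d by "dividing the differences between change scores of both groups across time by the pooled SD of both groups at baseline". It names neither a baseline covariate nor a constraint that the arms share a baseline mean. It commits to analysing everyone randomised, with missing follow-up treated as missing at random.

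The Sample size section states the target effect: "We considered a moderate effect size to be clinically meaningful (*f*=0.25), within a repeated measure analysis of variance". Power is set at 0.80 and the significance level at 0.05. The correlation between baseline and 3-month scores is taken as 0.50, which the section calls "an assumed strong association". The total is 154, including 16% attrition. Under Design, allocation is 1:1 and unstratified, and it takes place after the pre-assessment. Table 1 shows PG-13 and all six secondary scales collected at baseline and at 3 months. The 6- and 12-month measurements are for the intervention group only.

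**The concern.** The waitlist arm contributes only a baseline and a 3-month value, so the randomised comparison rests on two time points. With a free condition term, the condition × time coefficient is then the difference in mean change. It subtracts any chance baseline difference in full, although regression to the mean would carry only a fraction r of it through to 3 months. Because baseline is measured before randomisation, the arms have equal baseline means in expectation. The data can therefore be used more efficiently by adjusting for baseline.

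Two things are at stake for PG-13 and for each of the six secondary outcomes: the width of the confidence interval (and so the power), and how far the estimate moves when the arms happen to start apart.

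**Working it through.** **Inputs.** From the Sample size section: f=0.25, r=0.50, α=0.05, power 0.80, attrition 16%, N=154. From Design: 1:1 allocation, so 77 per arm. Completers: 154 × 0.84 = 129.4, or 64.7 per arm. For two equal groups d = 2f = 0.5. Assumed here, because the documents give no SDs: equal SDs at baseline and 3 months, set to 1. Participants are treated as independent.

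**Reproducing the plan's figure.** Noncentral F with 1 and N−2 degrees of freedom and noncentrality f²N gives power 0.8015 at N=128. Then 128/0.84 = 152.4, so 153, or 154 with equal arms. The plan's total is reproduced. Entering r=0.50 in the noncentrality does not reproduce it: the between-factor form needs 98 (117 after attrition) and the interaction form 34 (41 after attrition). So f=0.25 acts as d=0.5. At r=0.50 this is the same on the raw scale and the change scale, because the SD of change is √(2(1−0.5)) = 1.

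**Variance per participant.**
- Change: 2(1−r) = 2(0.5) = 1.00. This is no better than ignoring baseline.
- Baseline-adjusted: 1−r² = 1−0.25 = 0.75.
- Ratio: (1+r)/2 = 0.75, a 25% reduction.

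**Power at d=0.5 with 64.7 completers per arm (noncentral t).**
- Change: SE = √(2×1.00/64.68) = 0.176; power 0.81.
- Adjusted: SE = √(2×0.75/64.68) = 0.152; power 0.90.
- Change contrast from a likelihood model that also uses dropouts' baselines: variance 2[(1−r²)/64.68 + (1−r)²/77] = 2[0.01160 + 0.00325] = 0.0297; power 0.82 (0.83 by normal approximation).

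The gain is therefore about 8–10 points. A simulation of 20,000 trials with 64 per arm gave 0.802 against 0.898. For 80% power the adjusted analysis needs 98 completers, against 128.

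**Sensitivity to r (change against adjusted, equal SDs).**

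| r | Change | Adjusted |
|---|---|---|
| 0.3 | 0.66 | 0.84 |
| 0.4 | 0.73 | 0.87 |
| 0.5 | 0.81 | 0.90 |
| 0.6 | 0.88 | 0.94 |
| 0.7 | 0.95 | 0.98 |

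**Sensitivity to the SDs.** Entry requires PG-13 above 16, so the baseline SD may be the smaller. With baseline SD k times the 3-month SD and the effect held at 0.5 of the 3-month SD, the change variance is 1 + k² − 2rk. At r=0.5:
- k=0.9: variance 0.91; 0.84 against 0.90, a gain of 6 points.
- k=0.8: variance 0.84; 0.87 against 0.90, a gain of 3 points.

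At r=0.7 and k=0.8 the gain is practically nil (0.97 against 0.98).

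**Chance imbalance.** Given a baseline difference D between arms, the change contrast has expectation effect − (1−r)D. With 77 per arm, the SD of D is √(2/77) = 0.16, so its 95% range is about ±0.32 SD. At r=0.5 the estimate moves by up to 0.5 × 0.32 = 0.16 SD, about a third of d=0.5. If the app arm starts with the higher grief score, the benefit is overstated; if it starts lower, understated. Baseline adjustment removes this shift.

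**The case against.** The strongest reply is that this is a preference for efficiency and not an error. The trial was sized on a repeated-measures analysis and tests condition × time, so design and analysis agree. The contrast is unbiased over randomisation and delivers the 80% it claims. All of that stands. What remains is that the protocol fixes a form that gives up precision already paid for, since the baseline scores are collected anyway.

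A second reply is that the article condenses its model and that the change-score sentence defines only a supplementary effect size. That is fair as far as it goes: the test is fixed by the condition × time sentence. But that sentence, read with the definition of d, describes a change contrast and no baseline adjustment, so this is a stated choice rather than an omitted detail.

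The size is also open to challenge. Ten points is the upper end at r=0.50; using dropouts' baselines, a higher r or a smaller baseline SD all reduce it. This stands and is carried into the verdict.

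A reader might further infer that a change contrast contradicts the Abstract's "The primary outcome will be prolonged grief symptoms at the 3 months follow-up". It does not. Under randomisation both contrasts target the same 3-month difference, and the primary hypothesis in the Introduction is itself worded as a decrease.

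**Conclusion.** The point holds as a worthwhile improvement, not as a fault in validity. The planned contrast is sound and adequately powered on its own terms. At r=0.50 and d=0.5 with about 129 completers and equal SDs, baseline adjustment raises power from about 0.81–0.82 to 0.90. The gain is larger at lower r. It falls to 3–6 points at r=0.50 if the baseline SD is 0.8–0.9 of the 3-month SD, and to about 2 points at r=0.7 with equal SDs. Adjustment also removes the shift caused by chance baseline imbalance.

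All these powers assume independent participants. The Design section places a second parent in the first parent's arm, so within-couple correlation would alter both figures. A reader might infer that the gain makes up for power lost to couples. The documents give neither the number of couples nor a within-couple correlation, so that cannot be claimed.

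**What to change.** State the primary estimate as the between-group difference in PG-13 at 3 months, adjusted for baseline PG-13. Two routes fit the existing commitments:

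- A longitudinal mixed model that constrains the baseline means to be equal across arms. It keeps all randomised participants under missing at random.
- ANCOVA with multiple imputation of missing 3-month values. ANCOVA on completers alone would drop participants and conflict with the commitment to analyse everyone randomised.

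Use the same form for each of the six secondary outcomes with its own baseline. Compute the between-group d as the adjusted difference divided by the pooled baseline SD. Fix the choice before outcomes are compared between arms, since picking between change and adjusted estimates afterwards would be data-driven.

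No new data, visits or participants are needed. The cost is a change of wording and, on the ANCOVA route, specifying the imputation model.
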